## Abstract

**Background:**

Depression is a common and disabling condition. Since 2001, Chile has had a national program for depression in primary care and universal access to treatment for depressed people over the age of 15. There are National Guidelines to treat depression but no training program exists. The aim of the present study protocol is to measure the effectiveness of a comprehensive technology-assisted training and supervision program to enhance depression management in primary care.

**Methods and design:**

This is a two-arm, single-blind, cluster randomized controlled trial to compare the efficacy of the program versus usual care to treat depression in primary care clinics. In total, 434 depressed persons 18 to 65 years of age, recruited from four primary care clinics located in Santiago, will participate in the study.

**Discussion:**

In order to ensure the quality of interventions supported by the national program for depression in Chile, it is desirable to have training programs of proven effectiveness.

**Trial registration:**

NCT02232854, registered on 2 September 2014.

## Background

Worldwide, depression is one of the most common and disabling psychiatric disorders. By 2020, depression is projected to be the second highest cause of disability in both sexes. It is a public health problem as a result of its high prevalence, duration, and recurrence rates [1].

In Chile, prevalence studies carried out in the general population reported a point prevalence of 5.5 % for depressive episodes, according to the ICD-10 criteria [2], and a 6-month prevalence of 4.7 % for major depressive disorder [3]. Studies carried out in primary care reported prevalence rates of around 30 % [4, 5].

Depression can be treated effectively with low-cost antidepressants or psychological interventions. For people with persistent sub-threshold depressive symptoms or mild depression, low-intensity psychosocial interventions should be used, and for moderate or severe depression, a combination of antidepressant medication and a high-intensity psychological intervention are recommended. Stepped-care and collaborative models provide a framework for integration of drug and psychological treatments and help to improve rates of adherence to treatment [6, 7].

In Chile, a randomized controlled trial to treat depression demonstrated the effectiveness of a stepped care program in primary care clinics. The stepped care program included a structured psychoeducational group led by social workers and nurses, a systematic monitoring of clinical progress, and structured pharmacotherapy for patients with severe or persistent depression that was executed by trained general practitioners. The results showed a large and significant difference in favor of the stepped care program compared with the usual care across all assessed outcomes, and this difference remained stable over a period of 6 months. This program was more effective and only marginally more expensive than usual care for the treatment of depressed women in primary care. Women receiving the stepped-care program had an average of 50 additional depression-free days over 6 months relative to patients who received usual care [8, 9].

Since 2001, Chile has had a program for the detection, diagnosis, and treatment of depression in primary care clinics. It recommends algorithms for diagnostic evaluation, delivery of psychosocial interventions and medications, consultations with specialists, follow-up visits, and criteria for referral to secondary care. All persons with depression have to be treated in primary care unless they have psychosis, bipolar disorder, high suicidal risk, or a lack of response to two courses of treatment with two different antidepressants at therapeutic doses, plus psychosocial intervention [10].

In 2006, depression was incorporated into the national health reform, thus ensuring universal access to treatment for depressed individuals 15 and older [11], the majority of whom are treated by primary care teams [12]. Since 2009, the Ministry of Health has published two Clinical Guidelines for depression treatment, but no training program has yet been recommended [10, 13].

An evaluation of the depression program carried out at seven primary care clinics in two regions of Chile demonstrated that diagnoses of the severity of illnesses were inaccurate, that severity of depressive episodes was underestimated, that treatments were not indicated according to the severity of the illness or according to guidelines, that adherence to treatment was insufficient − higher for pharmacological treatment and lower for individual psychotherapy and group psychoeducation − and that patient dropout from the program was around 60 % [14, 15].

International evidence indicates that, despite the high prevalence of depression and availability of effective treatments, the diagnosis and treatment of depression by general practitioners do not follow clinical guidelines and that these guidelines do not always include training [16, 17].

Training can improve the detection, diagnosis, and treatment and could lead to better patient outcomes, although studies have shown that training alone does not result in improved outcomes [18, 19].

There is abundant literature on the effectiveness of collaborative care on depression [20]. Systematic literature reviews of strategies employed to improve mental health patient outcomes reported that the most effective interventions incorporate clinician education, nurse case management, a greater integration between primary and secondary care [21], and quality measures to improve results [22].

For these reasons, we believe that a comprehensive technology-assisted training and supervision program can improve depression management in primary care clinics in Santiago, Chile.

## Methods and design

This is a two-arm, single-blind (blinded only to outcome evaluator), cluster randomized controlled trial, which will compare the effectiveness of a comprehensive technology-assisted training and supervision program for depression management versus usual depression care in primary care clinics in Santiago, Chile.

### Aims and hypotheses

#### General aim

To carry out a cluster randomized controlled trial to compare the efficacy of a comprehensive technology-assisted training and supervision program versus usual care to treat depression in primary care clinics in Santiago, Chile.

### Specific aims

To compare the level of depressive symptoms of adults treated for depression through a comprehensive technology-assisted training and supervision program versus usual care in primary care clinics.To compare patients’ adherence to a comprehensive technology-assisted training and supervision program versus usual care in primary care clinics.To compare health-related quality of life of adults suffering depression treated in a comprehensive technology-assisted training and supervision program versus usual care in primary care clinics.To compare clinical outcomes of patients treated in a comprehensive technology-assisted training and supervision program versus usual care in primary care clinics.To compare use of health care services by patients treated in a comprehensive technology-assisted training and supervision program versus usual care in primary care clinics.To compare the rate of treated depressed cases by teams participating in a comprehensive technology-assisted training and supervision program versus those following only the usual care approach in primary care clinics.

### Hypotheses

Adults receiving the intervention will reach clinical remission, given by a score of 10 or less in the PHQ-9, with a difference of 20 % when compared with the group receiving the usual care, 3 and 6 months after randomization.Adults participating in the intervention program will have (significantly) better adherence to treatment than those receiving usual care, 3 and 6 months after randomization.Adults participating in the intervention program will have significantly better quality of life than those receiving usual care, 3 and 6 months after randomization.Adults participating in the intervention program will have significantly better clinical outcomes than those receiving usual care, 3 and 6 months after randomization.Adults participating in the intervention program will have significantly greater service use than those receiving usual care, 3 and 6 months after randomization.Primary care teams participating in the intervention program will treat more depressed cases than those that are only in the usual care program, during a 1-year timeframe.

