### Outcome measures

#### Primary outcome measure

Depressive symptoms will be assessed as the primary outcome, using the Patient Health Questionnaire-9 item (PHQ-9) [23]. The PHQ-9 is a nine-item self-administered measure of depression, with documented reliability and validity in the sample population [24]. It is a dual-purpose instrument that, with the same nine items, can establish provisional depressive disorder diagnoses, as well as determine depressive symptom severity. Major depression is diagnosed if five or more of the nine depressive symptom criteria have been present at least “more than half the days” in the past 2 weeks, and one of the symptoms is depressed mood or anhedonia. As a severity measure, the PHQ-9 score ranges from 0 to 27 [23]. A score equal to 10 points or higher is indicative of major depressive syndrome. Severity can be categorized as follows: healthy (1–5), subclinical depressive symptoms (6–10), mild depression (11–15), moderate depression (16–20), and severe depression (21–27) [22]. In primary care studies, the questionnaire has a sensitivity for major depression of 88 %, specificity of 88 %, and positive likelihood ratio of 7.1 [23]. It was validated in a Chilean population [25].

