### Sample size

Sample size calculation was done based on two studies previously carried out in Chile [36, 15]. A randomized clinical trial that compared pharmacotherapy monitored by telephone with usual care in primary care clinics in Chile found a recovery rate for depressive disorders of 62 % in the intervention group versus 38 % in the control group [36], having an effect size of 20 %. Since the current study protocol aims to test whether the intervention is better than usual care, a one-sided test is appropriate to detect an effect. Moreover, it is expected that the intervention will have a favorable effect ruling out the possibility of a statistically significant negative effect. To detect a difference of 20 %, in a one-sided model, with an alpha of 5 % and power of 80 %, 152 depressed persons, 76 in each group (intervention and control), will be required for the study. Using a database from another study comprising 201 persons treated for depression in seven primary care clinics [15], an intraclass correlation coefficient (ICC) of 0.03839 was estimated. Therefore, a design effect of 2.42 was determined, based on the previously calculated ICC and the use of four clusters (primary care clinics). After applying the design effect, the sample needed increased to 368 depressed persons. Considering a retention rate of approximately 85 %, 434 depressed cases will be required for the study, hence 109 cases in each of the four primary health care clinics.

Finally, a group of four primary health care clinics was chosen for two reasons: the usual flow of patients with depression presenting at each of the participating primary care clinics, which allows for a high number of potential participants per clinic, and financial constraints restricted the number of clusters, since having more primary care clinics would put in jeopardy the feasibility of the study.

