### Data analysis

Data analysis will be performed using SPSS software [37], with which scores of the used scales will be calculated. Data and presentation of the results will be in accordance with CONSORT guideline for randomized clinical trials [38] as well as its extensions to cluster and non-pharmacological interventions, with the primary comparative analysis being conducted on an intention-to-treat basis. Initially, we will conduct descriptive analysis to assess the balance between the two groups. The primary analysis will employ multivariable linear regression to investigate differences in mean symptom scores (the primary outcome measure) between groups at 3 and 6 months after randomization, adjusting for baseline outcome variables if imbalances are identified. Sensitivity analysis based on different assumptions will be conducted to investigate the potential effects of missing data. Similar analysis will be carried out for secondary outcome measures.

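### Hypothesis 1 and the sample size concern a 20-point difference in proportions, but the declared primary analysis compares mean PHQ-9 scores, so the stated 80 % power belongs to a different endpoint

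*Protocol article*

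**What the plan says.** Two parts of the protocol article speak of a proportion:

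- Hypotheses, first item: "Adults receiving the intervention will reach clinical remission, given by a score of 10 or less in the PHQ-9". The gap claimed over usual care is 20 %, at both follow-up times.
- Sample size: an earlier Chilean trial is cited for a "recovery rate for depressive disorders of 62 % in the intervention group versus 38 % in the control group". The trial is then sized for a difference of 20 %, one-sided, with alpha 5 % and power 80 %. This gives 76 per group, 368 after the design effect and 434 after allowing for retention.

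Three parts speak of a score:

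- Specific aims, first item: "To compare the level of depressive symptoms of adults treated for depression".
- Primary outcome measure: depressive symptoms on the PHQ-9, scored 0 to 27.
- Data analysis: "multivariable linear regression to investigate differences in mean symptom scores (the primary outcome measure) between groups at 3 and 6 months".

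Remission is not listed under primary, secondary or other outcomes, and the Data analysis section describes no model for a proportion.

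**The concern.** The hypothesis and the power calculation rest on one endpoint, and the declared primary outcome and its analysis on another. A mean difference depends on the whole distribution of scores; a remission gap depends on how many patients cross one cut. Neither determines the other without further assumptions. Two things are at stake. The quoted 80 % power gives the reader no information about the analysis that will decide the trial. And a result on means, whichever way it falls, leaves the 20-point remission claim unanswered. If the two endpoints disagreed, the Hypotheses section would support one headline and the Data analysis section another.

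**Working it through.** **Inputs from the Sample size section.** One-sided alpha 5 %, power 80 %, difference 20 % (read as percentage points), 76 per group, ICC 0.03839, four clinics, design effect 2.42, 368 after the design effect, 85 % retention, 434 in total. **Not given anywhere:** the base rate for the 20-point difference, a target mean PHQ-9 difference, and an SD.

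**1. Reproducing the protocol's figure.** For two proportions,

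n per group = [1.645 √(2p̄(1−p̄)) + 0.842 √(p₁(1−p₁) + p₂(1−p₂))]² / (p₁−p₂)².

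- With 58 % vs 38 % (assumed base rate): [1.645 × 0.7065 + 0.842 × 0.6922]² / 0.04 = 3.045 / 0.04 = 76.1.
- Rounded up, 58/38, 60/40 and 62/42 give 77, and 55/35 gives 76. The arcsine formula gives 76.1 to 76.2 for the first three pairs.
- The cited 62 % vs 38 % is a gap of 24 points. It gives 53 per group one-sided, and 76 only if two-sided with a continuity correction, which is not what the text describes. That too would be a comparison of proportions.
- Design effect: 152/4 = 38 per clinic; 1 + (38 − 1) × 0.03839 = 2.42; 152 × 2.42 = 367.8, so 368; 368/0.85 = 432.9, against 434 stated (a rounding difference).

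The chain reproduces as a two-proportion calculation. With no SD and no mean difference in the document, it cannot be rebuilt as a calculation for means.

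**2. Power of the declared analysis.** This is undefined from the document. As an illustration, take the protocol's own effective size, 184/2.42 = 76 per arm, one-sided 5 %, normal approximation:

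power = Φ(δ √(76/2) − 1.645) = Φ(6.164 δ − 1.645), with δ the assumed standardised difference.

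- δ = 0.2: Φ(−0.412) = 34 %
- δ = 0.3: Φ(0.204) = 58 %
- δ = 0.4: Φ(0.821) = 79 %
- δ = 0.5: Φ(1.437) = 92 %

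The difference detectable with 80 % power is (1.645 + 0.842) × √(2/76) = 0.40 SD. That is 1.6, 2.0, 2.4 or 2.8 PHQ-9 points for an assumed SD of 4, 5, 6 or 7.

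**3. Can the 20 points be turned into a mean difference?** Only by assuming 38 % vs 58 %, normal scores with equal SDs, and that recovery in the cited trial means a PHQ-9 of 10 or less. Then:

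- Shift = Φ⁻¹(0.58) − Φ⁻¹(0.38) = 0.202 + 0.305 = 0.507 SD.
- Sample size before clustering: 2 × (1.645 + 0.842)² / 0.507² = 12.37 / 0.257, about 48 per group.
- Power at 76 per arm: Φ(6.164 × 0.507 − 1.645), about 93 %.
- In reverse, the detectable 0.40 SD would correspond to Φ(−0.305 + 0.403) = Φ(0.098) = 53.9 % in remission against 38 %, about 16 points rather than 20.

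So even under the most convenient model, the same sample size implies different targets on the two scales.

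**4. A separate matter that affects both endpoints.** The design effect uses 38 patients per clinic, although 368/4 = 92 are to be analysed. With 92 it is 1 + 91 × 0.03839 = 4.49, which leaves an effective 184/4.49 = 41 per arm. The figures in steps 2 and 3 keep the protocol's 2.42 and are optimistic to that extent.

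**The case against.** The best defence is that the primary endpoint is not in doubt. The first specific aim, the Primary outcome measure section and the Data analysis section agree on symptom level, and the last states outright that the mean score is primary. On this view hypothesis 1 is loosely worded, and sizing on a proportion may even be conservative. Much of this stands, and it rules out several stronger readings that a reader might infer:

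- **That the investigators are free to choose an endpoint after seeing the data.** The Data analysis section names the mean score as primary, so such freedom is not shown. What remains is a hypothesis and a planning basis that do not match it.
- **That remission will never be tested.** The article describes no such test, but it is a condensed account, and a separate analysis plan may contain one.
- **That the trial is underpowered for means.** Power depends on a difference and an SD that the document does not give. Under the assumptions in step 3 of the working it would be above 80 %.
- **That the mean is the more efficient endpoint, or that about 0.5 SD is its design target.** Both need the assumed 58 %, equal-SD normal scores on a bounded 0 to 27 scale, and the unstated link from recovery to the PHQ-9 cut.

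The defence does not remove the mismatch. An additional remission model in an analysis plan would not make the stated 80 % power apply to the mean comparison, nor would it make hypothesis 1 agree with the declared primary outcome.

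**Conclusion.** The point holds as an inconsistency between sections of the protocol article. Hypothesis 1 and the sample size are in proportions, the primary outcome and analysis are in means, and no target mean difference or SD connects them. The stated 80 % power does not describe the primary analysis, and a result on means cannot answer hypothesis 1 as worded. The range of 34 % to 92 % shows how far power depends on what is left unstated; it is not an estimate of this trial's power. It rests on assumed standardised differences of 0.2 to 0.5, the protocol's own design effect and a one-sided 5 % test. This should be fixed, but it does not invalidate the design: the declared primary analysis can be carried out as it stands.

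**What to change.** Make the Hypotheses, Sample size and Data analysis sections agree. Either route resolves the contradiction:

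- **Keep mean PHQ-9 as primary.** Reword hypothesis 1 as a mean difference. Restate power for a stated and justified mean difference and SD, with a design effect based on the number analysed per clinic. Name remission as a secondary endpoint, analysed with adjustment for clustering and reported as a risk difference with a confidence interval, to be set against the 20 points.
- **Make remission primary.** Give it a matching cluster-adjusted analysis, state the base rate behind the 20-point difference, and move the mean score to a secondary position.

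In both cases reconcile the PHQ-9 score of 10. Under Hypotheses it counts as remission, while the Primary outcome measure section treats 10 and above as pointing to major depression and also places 10 in its subclinical band. The remission variable is not well defined until that is settled.

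The cost is rewording three sections and the cut-off statement, one revised power calculation and one additional model. No new data are needed, because the PHQ-9 is already collected at 3 and 6 months.

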### Setting and population

Adults between 18 and 65 years of age attending four primary care clinics located in two low-income municipalities of Santiago, Chile.

### Inclusion and exclusion criteria

Depressed adults aged between 18 and 65 years of age attending primary care clinics will be invited to participate. Informed consent will be obtained from each participant.

Depression will be assessed with the Patient Health Questionnaire-Nine items (PHQ-9) and the Mini-International Neuropsychiatric Interview (MINI). Individuals currently receiving treatment for depression and/or those without access to a telephone will be excluded.

### Intervention arm

The intervention arm includes a 16-h training program for primary care teams (physicians, psychologists, social workers, nurses, midwives, and occupational therapists) to ensure compliance with the Clinical Guidelines for the Treatment of Depression, issued by the Chilean Ministry of Health [10]. The workshop will include a seminar on the detection, diagnosis, and treatment of depression; discussion of clinical cases; and role-playing to enhance clinical skills and to apply problem-solving techniques. Finally, trained primary care teams will undergo an Objective Structured Clinical Examination (OSCE) for evaluation.

After the training, a focus group between primary health care teams and study researchers will be held in order to address barriers to the implementation of clinical guidelines. In order to develop a comprehensive supervision program, trained administrative staff will contact patients from a call center to support treatment adherence, and a psychiatrists will supervise the primary care team, using a web-based platform.

### Control arm

The control arm will receive treatment as usual − all the interventions that are guaranteed for persons with depression from the primary care clinics and if needed referral to the specialized psychiatric service, as indicated by the national depression program. Professionals will be told to follow the Clinical Guidelines for the Treatment of Depression [10].

### Outcome measures

#### Primary outcome measure

Depressive symptoms will be assessed as the primary outcome, using the Patient Health Questionnaire-9 item (PHQ-9) [23]. The PHQ-9 is a nine-item self-administered measure of depression, with documented reliability and validity in the sample population [24]. It is a dual-purpose instrument that, with the same nine items, can establish provisional depressive disorder diagnoses, as well as determine depressive symptom severity. Major depression is diagnosed if five or more of the nine depressive symptom criteria have been present at least “more than half the days” in the past 2 weeks, and one of the symptoms is depressed mood or anhedonia. As a severity measure, the PHQ-9 score ranges from 0 to 27 [23]. A score equal to 10 points or higher is indicative of major depressive syndrome. Severity can be categorized as follows: healthy (1–5), subclinical depressive symptoms (6–10), mild depression (11–15), moderate depression (16–20), and severe depression (21–27) [22]. In primary care studies, the questionnaire has a sensitivity for major depression of 88 %, specificity of 88 %, and positive likelihood ratio of 7.1 [23]. It was validated in a Chilean population [25].

